**Objective:**

This protocol describes a longitudinal study designed to examine real-world changes in risk of suicide across multiple assessment domains. Specifically, the study involves following adults known to be at high risk of suicide after discharge from inpatient psychiatric care using self-report, interview, actigraphy, and behavioral methods to identify proximal contributors to suicidal thoughts and behaviors. First, we hypothesize that negative affective experiences, which are featured in most major suicide theories, will comprise a latent factor indicative of psychache (emotional pain), which will predict increases in suicidal thinking over time. Second, we hypothesize that poor inhibitory control in the context of negative affective stimuli, as well as emotion-related impulsivity, will predict the transition from suicidal thinking to suicidal behavior over time. Third, we hypothesize that short sleep duration will precede within-person increases in suicidal ideation as well as increased odds of suicidal behavior among those reporting suicidal thoughts.

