Although a plethora of cross-sectional studies have shown associations between these negative affective experiences and SI [26-33], little work is available on negative affective experiences as prospective predictors of SI. Longitudinal work has primarily examined negative affective experiences as predictors of SI over months or years [34,35] rather than as predictors of within-person short-term changes in SI. Recent ecological momentary assessment (EMA) research has demonstrated that many negative affective experiences fluctuate markedly at the within-person level, as does SI [15,36-40]; however, these studies have been limited by small sample sizes [15,36], short durations [37,38], and use of analog (community) samples [39-41]. Furthermore, negative affective experiences tell us little about which people with suicidal thoughts will go on to attempt, or die by, suicide, a central issue across ideation-to-action models.

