### Hypotheses

The goal of this study is to integrate examination of affective, cognitive, and physiological risk factors for short-term changes in suicidal thinking and suicidal behaviors among adults known to be at high risk within an ideation-to-action framework. To that end, our hypotheses are as follows:

Hypothesis 1a (H1a): within-person increases in affective suicide risk factors conceptually related to psychache (negative affective experiences) will individually precede within-person increases in SI.Hypothesis 1b (H1b): negative affective experiences will co-occur in daily life such that they are best conceptualized as indices of a single latent construct capturing emotional distress (psychache), which will itself predict short-term increases in SI.Hypothesis 2a (H2a): among those with SI, higher baseline self-reported emotion-related impulsivity will predict greater odds of SA over follow-up.Hypothesis 2b (H2b): among those with SI, poorer baseline behavioral indices of inhibitory control in the context of negative affective stimuli will predict greater odds of SA over follow-up. We also predict that, among those with current SI during EMA, lower EMA-assessed inhibitory control will prospectively predict subsequent SA.Hypothesis 3a (H3a): during the EMA protocol, short sleep duration will predict within-person increases in SI.Hypothesis 3b (H3b): during the EMA protocol, short sleep duration will predict greater risk of next-day SA among those with SI.Exploratory hypothesis 3c (H3c): the within-person effects of short sleep duration on SA will be mediated by within-person changes in inhibitory control assessed during EMA.

A visual depiction of these hypotheses is provided in Figure 1.

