## Methods

### Project Overview

This is a single-group, repeated-measures (within-persons) observational study following adults with recent STB receiving inpatient psychiatric treatment (N=130). An ethnically diverse sample of participants will be recruited during inpatient psychiatric treatment in Lubbock, Texas, United States, based on past week STB. Eligible and interested participants will then complete the informed consent process, self-report surveys, clinical interviews, a computer task assessing cognitive inhibition, and a debriefing procedure. After discharge from inpatient care, participants will engage in a 4-week (28-day) EMA protocol that involves receipt of 7 signal-contingent self-report survey prompts per day between participants’ self-reported wake times and bedtimes. Participants will also be prompted to complete an abbreviated version of the cognitive inhibitory control task after each survey and asked to wear an actigraphy device for the 28-day follow-up period to assess objective indicators of sleep. Participants will be invited to complete a remote (phone or videoconference) follow-up interview assessing recent STB at 4 weeks and 8 weeks after discharge.

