For H3a and H3b, the models are identical to those for H1a, H1b, and H2B, except that analyses are conducted at the day level (*t*=28) to examine the effects of sleep. Previous studies have shown significant effects for the impact of sleep quality on next day SI (β=–.11) [79]. Although examination of within-day fluctuations in inhibitory control is exploratory (H3c), prior work showing large differences in inhibitory control between self-harm and control groups (Cohen *d*=0.84) [70] allowed us to conservatively estimate how day-level inhibitory control predicts SI and SA. Thus, we repeated our simulations outlined for H1a using *t*=28 and single predictors for sleep (H3a and H3b) and inhibitory control (H3c) in separate models. Models converged across repetitions, indicating that with n=100, the study is well powered (>0.8) to find standardized regression effects as low as 0.15 (representing small effects) for the within-person regressions of SI and SA on day-level inhibitory control or sleep disturbance.

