**All surveys**		
	Current suicidal ideation	2
	Current urges for nonsuicidal self-injury	2
	Current negative affect	6
	Current positive affect	2
	Current hopelessness	1
	Current agitation	2
	Current emotional pain	2
	Current defeat	2
	Current entrapment	2
	Current self-criticism	2
	Current suicide capability	4
	Current physical pain interference	1
	Current belongingness	2
	Current burdensomeness	2
	Current perceived emotional support	2
	Current perceived practical support	2
	Since last survey: suicidal behavior	1
	Since last survey: nonsuicidal self-injury	1
	Since last survey: stressors	3
	Since last survey: complimented or praised	1
	Since last survey: alcohol use	2
	Since last survey: drug use	4

At baseline, participants will also be provided with the actigraphy device (wActiSleep-BT; ActiGraph, LLC) and instructed on how to wear it during the follow-up period. Participants will be asked to wear the device as much as possible for 28 days after discharge. The device continuously records activity through accelerometer (approximately 30-hertz data sampling with timestamps) with a single charge typically exceeding 28 days [96]; however, participants will also be provided with a charger and asked to charge the device at least twice during follow-up at times when the watch would not otherwise be worn, such as when bathing. The device continuously records data to provide valid scores for a variety of indices, including sleep duration, sleep onset latency, total awakenings, length of awakenings, overall sleep efficiency, intensity of movement during sleep awakenings, and light exposure during sleep [97]. Participants will be provided with a self-addressed, postage-paid envelope to return the actigraphy device, charger, and loaner phone (if applicable) to the research team after study completion.

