For H2a, we will estimate the effects of baseline emotion-related impulsivity and inhibitory control on odds of SA over follow-up, controlling for between-person differences in SI severity. To do this, person-mean estimates of SI and person-maximum estimates of SA (yes or no) will be calculated using EMA data. SA can then be predicted by baseline emotion-related impulsivity and inhibitory control scores using logistic regression analysis, controlling for participants’ SI severity. For H2b, we will then test whether within-person changes in state inhibitory control precede subsequent SA among individuals reporting SI. Using a 2-level random slope model, we will model time *t* inhibitory control (controlling for inhibitory control measured at time *t–*1) as a predictor of time *t*+1 SA, controlling for time *t* SI.

For sleep-related hypotheses, we will use 2-level random slope models, as described previously, but in which survey-level data on SI and SA have been pooled to create day-level variables (because sleep varies at the daily, but not survey, level). For H3a, we will use person-mean–centered total sleep time on day *d–*1 to predict next-day (day *d*) SI, controlling for day *d–*1 SI. Models for H3b will parallel those used to test H2a, whereby total sleep time on day *d*-1 will be used to predict next-day SA (day *d*), controlling for day *d* SI. For H3c, we will test whether the sleep-SA association (H3b) is mediated by within-person changes in inhibitory control. Building on the H3b model, we will add in the effect of sleep on day *d–*1 predicting inhibitory control on day *d*. To ensure that we are capturing sleep-related changes in inhibitory control, inhibitory control on day *d* will also be regressed on inhibitory control measured on day *d–*1. Finally, day *d* inhibitory control will be used to predict day *d* SA, controlling for day *d* SI. Indirect and direct effects will be calculated and tested for significance using the MPlus *model indirect* command.

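### H3a adjusts only for ideation pooled over the previous day, so evening ideation that shortens sleep and carries over can pass as a sleep effect

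*Protocol article*

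**What the plan says.** The hypothesis is directional in time. The Objective states that "short sleep duration will precede within-person increases in suicidal ideation", and the Hypotheses section that "during the EMA protocol, short sleep duration will predict within-person increases in SI".

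The Data Analysis Plan explains that in the sleep models "survey-level data on SI and SA have been pooled to create day-level variables (because sleep varies at the daily, but not survey, level". It does not name the pooling function. For H3a, person-mean-centred total sleep time on day *d*–1 is used to "predict next-day (day *d*) SI, controlling for day *d–*1 SI". No other SI term is stated. The same section has a general sentence about examining potential confounders, but it names none.

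The timing information exists. The Project Overview describes "receipt of 7 signal-contingent self-report survey prompts per day between participants’ self-reported wake times and bedtimes", and Table 2 lists "Current suicidal ideation" (two items) among the domains asked at every survey. Under Power Analyses, "analyses are conducted at the day level (*t*=28) to examine the effects of sleep".

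**The concern.** A claim that short sleep precedes a rise in SI needs prior SI removed as a common cause of sleep and of next-day SI. The SI most likely to disturb a night, and to be present the next morning, is SI near bedtime. One value summarising up to seven prompts since waking is only a proxy for it. What the proxy misses is credited to sleep, with the hypothesised sign: shorter sleep, more SI.

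The stated reason for pooling explains why sleep is a daily variable. It does not require discarding the timing of SI before sleep. H1a, by contrast, adjusts for SI at the immediately preceding survey. The article intends the sleep findings to inform suicide-specific sleep treatments (Dissemination Plan and Future Directions), so a slope that partly reflects evening SI would be misread.

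**Working it through.** **1. The plan's own figure.** The article states power above 0.8 for a standardized effect of 0.15 with n=100 and 28 days. For a continuous day-level outcome with one lag, power ≈ Φ(0.15 × √(100 × 27) − 1.96) = Φ(7.79 − 1.96) = Φ(5.83), above 0.99. The claim holds for H3a. The standard error is about 1/√2700 = 0.019, so a spurious slope of a few hundredths can matter.

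**2. Overnight gap.** Prompts fall in seven equal bins from 15 minutes after waking to bedtime (Intensive Longitudinal Protocol). Time in bed is assumed.
- 8 h: bin = (24 − 8 − 0.25)/7 = 2.25 h; mean gap from last to first prompt = 8 + 0.25 + 2.25 = 10.5 h, or 10.5/2.25 = 4.67 steps.
- 7 h: bin 2.39 h, gap 9.64 h, 4.0 steps.
- 6 h: bin 2.54 h, gap 8.79 h, 3.5 steps.

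A gap of 2 steps would need 2.75 h in bed, unless SI decays more slowly overnight than by day.

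**3. Bias when sleep has no effect.** Assume within-person SI has variance 1 and autocorrelation φ per prompt, *g* steps pass overnight, sleep correlates −*r* with last-prompt SI, pooling is by mean, and all surveys are answered.
- Covariance of the day mean with its last prompt: a = (1/7) Σ φ^k, k = 0 to 6.
- Variance of the day mean: v = (1/49)[7 + 2 Σ (7 − k) φ^k], k = 1 to 6.
- Standardized sleep slope, adjusting for the day *d*–1 mean: β = −r φ^g a (v − a²) / [(v − r²a²) √v].
- False confirmation ≈ Φ(|β|/SE − 1.96), with least-squares SE on 2,700 person-days (0.018 to 0.020 across cells).

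For φ = 0.6, 0.7, 0.8: a = 0.347, 0.437, 0.564 and v = 0.423, 0.518, 0.641.

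Example, φ = 0.7, r = 0.3, g = 2: β = −0.3 × 0.49 × 0.437 × 0.327 / (0.501 × 0.720) = −0.058; false confirmation Φ(0.058/0.0192 − 1.96) ≈ 86%. Simulations gave −0.059 to −0.062 and 85% to 87%. At g = 4.67, φ^g falls from 0.49 to 0.189, so β = −0.058 × 0.189/0.49 ≈ −0.022, with about 21% false confirmation (simulated: −0.023 and 29%, 150 runs).

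| r | g = 4 to 4.67: slope | false confirmation | g = 2: slope | false confirmation |
|---|---|---|---|---|
| 0.1 | −0.004 to −0.015 | 4–12% | −0.014 to −0.023 | 11–24% |
| 0.2 | −0.007 to −0.030 | 6–34% | −0.028 to −0.046 | 30–71% |
| 0.3 | −0.011 to −0.046 | 8–66% | −0.042 to −0.071 | 59–97% |

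Simulated ranges agree: −0.004 to −0.047 and 3% to 67% at 4 to 4.7 steps; up to −0.075 and 97% at 2 steps. At r = 0 the slope is 0. Pooling by daily maximum hardly changes the result: in a separate simulation at 0.2, −0.030 to −0.061 against −0.031 to −0.060 for the mean.

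**4. Effect of the fix.** Under these assumptions next-day SI is independent of sleep given last-prompt SI, so the slope becomes 0 (simulated: −0.001 to 0.001). At 64% response, with a 0.2 link and slow overnight decay, it falls from −0.057 to −0.023, −0.060 to −0.021 and −0.046 to −0.015, which are reductions of 60%, 65% and 67%. With item reliability of 0.8 as well, it falls from −0.055 to −0.032, −0.062 to −0.037 and −0.052 to −0.037: only 42%, 40% and 29%.

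**The case against.** The strongest reply is that every driver of the size is assumed. The documents give neither the autocorrelation of SI nor its evening correlation with sleep, and with no such link there is no bias. That stands, and it is why the size is a wide range. A reader might take the 2-step results, up to 97% false confirmation, as typical. The seven-bin schedule does not support that unless overnight decay is slow.

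Second, the article does not say which night belongs to day *d*–1. The night leading into day *d* is the natural reading of next-day prediction, but it is not confirmed. If the night ending on the morning of *d*–1 were meant, evening SI on *d*–1 would follow that sleep and this confounding would not arise. Pooled *d*–1 SI would then lie on the causal path instead.

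Third, lagged day-level adjustment is a common choice, and the plan promises to look at confounders. That general promise does not alter the model stated for H3a.

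Three stronger inferences go beyond the text. The Introduction says that "many negative affective experiences fluctuate markedly at the within-person level, as does SI", which means within person and not specifically within a day. H3a says that short sleep predicts or precedes increases; it does not claim to rule out SI disturbing sleep. The −.11 cited under Power Analyses is for sleep quality, whereas H3a tests total sleep time, so it is no direct yardstick for the spurious slope.

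**Conclusion.** The point holds on the night-before reading. The stated H3a model does not fully block the path from evening SI through shortened sleep to next-day SI, and the resulting error favours the hypothesis. With φ of 0.6 to 0.8, a correlation of −0.1 to −0.3 and a gap of about 4 to 5 steps, the spurious slope is about −0.004 to −0.05 and false confirmation about 3% to 67%, against 2.5% in that direction. At the weak end this is negligible; at the strong end it could decide the hypothesis. The calculations use ordinary within-person regression and not the planned Bayesian dynamic model. The missing covariate is a matter of specification, so changing the estimator would not by itself close the path.

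The documents do not show that H3a will be falsely confirmed, or that a real sleep effect is absent. They show that the planned adjustment cannot separate the two explanations as well as the collected data allow.

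**What to change.** In H3a, add SI at the last completed survey before the sleep period as a covariate, alongside or instead of pooled day *d*–1 SI. State that day *d*–1 sleep is the night between *d*–1 and *d*, if that is what is meant. Name the pooling function in the same sentence.

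The cost is one covariate that is already collected, and analysis begins only after data collection ends. The limit is that missed evening surveys make the last value less recent. At about 64% response the bias is reduced by roughly half to two thirds and not removed, and by less if the SI items are unreliable. Reporting the time from last survey to sleep, and a sensitivity analysis restricted to days with an evening survey, would show how much this matters. Modelling day *d* SI at survey level is also possible, but that is a different model and is not needed for this correction.

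### H3b and H3c adjust for ideation on the day of the attempt but not for ideation before the night, so pre-sleep ideation can appear as a sleep effect on attempts

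*Protocol article*

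**What the plan says.** All references are to the protocol article.

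- **H3b model (Data Analysis Plan).** Total sleep time on day d-1 "will be used to predict next-day SA (day *d*), controlling for day *d* SI". No SI term for day d-1 is listed. The text says the model parallels H2a, but H2a is a between-person logistic regression with no lag.
- **H3c model (Data Analysis Plan).** It builds on H3b: "day *d* inhibitory control will be used to predict day *d* SA, controlling for day *d* SI".
- **H3a model (Data Analysis Plan).** Person-mean-centred sleep on day d-1 is used "to predict next-day (day *d*) SI, controlling for day *d–*1 SI".
- **H2b model (Data Analysis Plan).** Inhibitory control at time t enters "as a predictor of time *t*+1 SA, controlling for time *t* SI".
- **Hypotheses.** H3a: "during the EMA protocol, short sleep duration will predict within-person increases in SI". H3b: "short sleep duration will predict greater risk of next-day SA among those with SI". The day on which SI must be present is not given.
- **Day-level data.** For the sleep models, "survey-level data on SI and SA have been pooled to create day-level variables".
- **General safeguard.** The Data Analysis Plan opens with an intention to examine confounders and include them where warranted. It names no variable.

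**The concern.** H3b needs to separate two explanations for a short night followed by an attempt: the short night contributed, or the person was already more suicidal the evening before and that both disturbed sleep and led to the attempt. The covariate that speaks to the second explanation is SI before the night. The plan has it in H3a and leaves it out of H3b and H3c.

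Day d SI is only a partial stand-in. By H3a it is itself expected to respond to sleep. It blocks the path from pre-sleep SI to SA only if everything that pre-sleep SI does to SA passes through day d SI, and only if day d SI is measured without error. An intention or plan formed the day before, or a coarse two-item momentary rating pooled to one daily value, would break one or both conditions.

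At stake is the H3b sleep coefficient, and with it the H3c mediation model built on top.

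**Working it through.** **Scale.** Power Analyses and Sample Size Considerations gives n=100, t=28 and power above 0.8 for a standardized effect of 0.15. Approximate power is Phi(0.15 × sqrt(2800 × p × (1-p)) - 1.96), where p is the share of days with the outcome.

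- p=0.15: Phi(0.15 × 18.9 - 1.96) = 0.81.
- p=0.10: Phi(0.15 × 15.9 - 1.96) = 0.66.
- p=10/2800=0.0036 (10% of 100 persons with one attempt each): 0.07.

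The protocol gives no daily attempt rate for H3b, so its power figure can be neither confirmed nor refuted. The 0.15 is used here only as a yardstick.

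**Closed form for the omitted covariate.** Put pre-sleep SI (S0), sleep (Q) and day d SI (S1) in SD units. Assume no sleep effect at all:

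- Q = g × S0 + noise
- S1 = 0.6 × S0 + noise
- logit P(SA) = constant + d1 × S0 + d2 × S1

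Leaving S0 out and keeping S1 gives Q an approximate coefficient of d1 × g × (1 - 0.36) / (1 - 0.36 × g²). The values of g, d1, d2 and 0.6 are assumptions; none is in the protocol.

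- g=-0.2, d1=0.5: 0.5 × (-0.128 / 0.9856) = -0.065.
- g=-0.3, d1=0.5: 0.5 × (-0.192 / 0.9676) = -0.099.
- d1=0: exactly 0.

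Large-sample simulation of this structure gave -0.06 to -0.10 for d1=0.5, and about 0 once S0 was added.

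**Independent simulation.** Logistic fits stood in for the Bayesian dynamic model. About 10-13% of days carried an attempt, and in the null scenarios the path from pre-sleep SI to sleep was -0.3. Entries are log-odds of SA per SD more sleep.

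| Scenario | Day d SI (plan) | Day d-1 SI only | Both |
|---|---|---|---|
| No sleep effect; prior SI acts only through day d SI, no measurement error | -0.002 | 0.000 | 0.000 |
| No sleep effect; direct prior-SI path 0.35 | -0.077 | 0.000 | +0.001 |
| No sleep effect; direct prior-SI path 0.7 | -0.144 | +0.002 | +0.003 |
| No sleep effect; no direct path, SI reliability 0.5 | -0.049 | -0.050 | -0.026 |
| No sleep effect; direct path 0.35, SI reliability 0.7 | -0.109 | -0.058 | -0.037 |
| Sleep acts only through SI (-0.2) | +0.012 | -0.123 | +0.012 |
| Sleep acts only through SI (-0.3); unmeasured shared cause of day d SI and SA | +0.185 | -0.178 | +0.174 |

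The spurious effect is 0.049/0.15 = 33% to 0.144/0.15 = 96% of the plan's detectable effect. Using both SI terms removes it when SI is well measured and reduces it otherwise.

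**False-positive rates at n=100, t=28.** At the attempt rates above, the direct paths of 0.35 and 0.7 gave 23.6% and 65.8% as planned, against 4.4% and 4.6% with both terms. With only about 10 and 13 attempt-days in total, the same two scenarios gave 5.4% and 6.4% as planned. The coefficient is still biased, but too imprecise for the bias to drive significance.

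**The case against.** The strongest defence is that holding day d SI constant is the question itself. The Abstract's third hypothesis, the Sleep Disturbances section and H3b all concern attempts among people with SI, and Sleep Disturbances names inhibitory control as the route. The route from sleep to SI has its own test in H3a. A reader might infer from the last two table rows that the plan wrongly hides an effect running through ideation. The documents do not support calling that an error: an effect given concurrent ideation is a fair reading of H3b. What stands is that the plan never says so, and that this reading still needs pre-sleep SI.

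A reader might also infer that day d SI should be replaced by day d-1 SI. In H3c that would do harm, because day d SI is concurrent with the mediator and controls confounding between inhibitory control and SA. In a simulation with no true inhibitory-control effect (assumed: day d SI lowers control by 0.2-0.3 and raises SA by 0.7), the swap produced a false effect of -0.08 to -0.14; the planned model gave +0.001 and -0.011.

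Three further objections are partly right.

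- **The false effect rests on assumed paths.** With a direct path of only 0.1, a check gave -0.01 to -0.02.
- **The timing is not spelled out.** If sleep on day d-1 is the night ending that morning, day d-1 SI follows the sleep, and adjusting for it would take out part of the effect: in one check a true total effect of -0.065 shrank to -0.020.
- **Safeguards exist.** The confounder clause, the autoregressive framework and the stressor items in every survey help, but none puts day d-1 SI into H3b or H3c.

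**Conclusion.** The concern holds in a limited form. H3b and H3c omit SI from before the night, and the covariate they do use is, by H3a, downstream of sleep. They can therefore return a sleep-SA association when sleep has no effect, illustratively -0.05 to -0.14 log-odds per SD.

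This requires that pre-sleep SI shortens sleep, and that it either affects SA beyond day d SI or that day d SI is measured with error. Without a direct route and with perfect measurement there is no bias. The path sizes are assumptions, and logistic regression replaced the planned Bayesian model, which should not change the direction. Conditioning on day d SI is not in itself shown to be a mistake. With the few attempts expected, lack of precision will limit H3b more than this bias will, but the omission is cheap to repair.

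**What to change.** 1. State which night sleep on day d-1 refers to. If it is the night between d-1 and d, pre-sleep SI is day d-1 SI; if it is the night before that, use SI from the day preceding it.
2. Add pre-sleep SI to the H3b and H3c equations for SA, alongside day d SI.
3. Describe the resulting coefficient as the effect of sleep given concurrent ideation, not as the total effect of a short night.
4. Report the H3b model with day d-1 SI only, without day d SI, as a companion total-effect estimate (again assuming the night between d-1 and d).
5. Keep day d SI in the H3c equation from inhibitory control to SA.
6. State the day that defines being among those with SI.

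The cost is one extra covariate, already constructed for H3a, with no new data. With few attempts it takes a little precision. It does not fully remove bias from poorly measured SI (-0.026 remained at reliability 0.5). Nor does it address an unmeasured shared cause of day d SI and SA (+0.174 with both terms), which is why the labelling and the companion estimate are needed.

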With respect to the criteria used for statistical inferences, these will vary by model and hypothesis. For logistic regression analyses (H2a), 2-tailed *P* values <.05 will be used as our criteria to make inferences. For dynamic structural equation models (H1a, H1b, H2b, H3a, H3b, and H3c), which use Bayesian estimation, 95% credibility intervals will be used; those intervals that do not include 0 will be evidence of a statistically significant effect. For multilevel exploratory factor analysis (H1b), we will examine unrestricted models with 1 to 7 factors at the within- and between-person levels, consistent with the components of the negative affective experiences construct. We will determine the most appropriate model fit based on an examination of model fit indices [101] as well as eigenvalues.

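### H3c pairs a random-slope model with a path-product style indirect effect; if both mediating slopes vary between persons, their covariance is left out

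*Protocol article*

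**What the plan says.** Everything here is in the protocol article. Under Hypotheses, H3c is labelled exploratory, and its target is that "the within-person effects of short sleep duration on SA will be mediated by within-person changes in inhibitory control assessed during EMA".

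The Data Analysis Plan sets the model class: "For sleep-related hypotheses, we will use 2-level random slope models, as described previously". H3c extends the H3b model with two paths. The first runs from the previous day's sleep to the day's inhibitory control, adjusted for the previous day's inhibitory control. The second is the path to suicide attempt (SA): "Finally, day *d* inhibitory control will be used to predict day *d* SA, controlling for day *d* SI". The estimator follows: "Indirect and direct effects will be calculated and tested for significance using the MPlus *model indirect* command".

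For the Bayesian models, H3c included, the inference rule is that "95% credibility intervals will be used; those intervals that do not include 0 will be evidence of a statistically significant effect".

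The text does not say which H3c slopes are random. It holds neither mediating path fixed and mentions no covariance between slopes.

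**The concern.** In a random-slope model each person i can have their own sleep-to-inhibitory-control slope a_i and their own inhibitory-control-to-SA slope b_i. H3c concerns mediation within persons, so the natural target is the average of a_i × b_i over persons. That average is not the product of the two average slopes unless the slopes are uncorrelated or one of them does not vary. A command that multiplies path coefficients returns the effect for a person with average slopes on both paths.

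The plan therefore names a model and an estimator that agree only under a condition it does not state. At stake are the H3c estimate and its 95% credibility interval, on which the significance call rests. If the slopes covary, the interval describes something other than the stated within-person mediated effect.

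**Working it through.** **No figure to reproduce.** The article gives no indirect effect, no power for an indirect effect and no slope covariance. The check is of the algebra and of how far the product could be off.

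**Inputs from the article**
- Model class, estimator and target of H3c: as set out above.
- Effect size 0.15 (standardized), n = 100, 28 days: Power Analyses and Sample Size Considerations. It applies to regressions of suicidal ideation (SI) and SA on day-level inhibitory control or sleep, so it can serve for b. No figure is given for sleep predicting inhibitory control.
- Random-effect variance: only an intercept variance of 0.3 is given.
- Proportion of participants with any SA: 10%, stated for H2a, so about 0.10 × 100 = 10 people.

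**Assumptions made here**
- Mean a = 0.15, set equal to mean b.
- The same slope SD for both paths, from 0.05 to 0.20.
- Slope correlation r from −0.5 to +0.5.
- The command returns a product of path coefficients. This is the ordinary sense of such a command; the article does not describe it.

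**Are both slopes random?** H2b already uses a two-level random slope model with state inhibitory control as a predictor of SA. That is the survey-level counterpart of the b path. The a path is added inside the random-slope class used for sleep. Both being random is the most natural reading, but it is not stated path by path.

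**Formula.** E(a_i b_i) = mean(a) × mean(b) + cov(a_i, b_i), with cov = r × SD².

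The product is 0.15 × 0.15 = 0.0225 in every row. Example: at SD 0.15 and r = +0.5, cov = 0.5 × 0.0225 = 0.01125. The average is 0.03375, and 0.0225 / 0.03375 − 1 = −33%.

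| Slope SD | r | Average indirect effect | Error of product |
|---|---|---|---|
| 0.05 | −0.5 / +0.5 | 0.0212 / 0.0238 | +6% / −5% |
| 0.10 | −0.5 / +0.5 | 0.0175 / 0.0275 | +29% / −18% |
| 0.15 | −0.3 / +0.3 | 0.0158 / 0.0292 | +43% / −23% |
| 0.15 | −0.5 / +0.5 | 0.0112 / 0.0338 | +100% / −33% |
| 0.20 | −0.5 / +0.5 | 0.0025 / 0.0425 | +800% / −47% |
| any | 0 | 0.0225 | none |

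**Simulation check.** Data were simulated for 10,000 persons over 28 days with a linear outcome and slope SD 0.20. The mean total effect minus the mean direct effect was compared with mean(a) × mean(b):
- r = +0.5: 0.0427 against 0.0220
- r = −0.5: 0.0024 against 0.0225
- r = 0: 0.0235 against 0.0230

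In a separate draw of 2,000,000 persons with b fixed and a random, both quantities were 0.0225. The product misses only when both slopes vary and covary.

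**The case against.** The strongest case against has four parts.

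1. The article names a model class, which a single random slope would satisfy. Which paths are random is detail that an article may leave to the preregistered material.
2. The article does not say what the command computes, or whether it can be used with random slopes.
3. All slope SDs and correlations are assumed, as is 0.15 for the a path.
4. With about 10 people expected to attempt, a random b slope would be weakly identified. If it were fixed, the product would be right.

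Much of this stands. It makes the point conditional and its size illustrative. It does not remove the point, because the article does more than omit detail: it fixes both the model class and the estimator, and the two fit only if one mediating slope is fixed or the slopes do not covary. If the command could not be used with random slopes, its sentence would still need replacing. The scarcity of attempters is a reason to state the choice.

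A reader might go further and infer that the plan certainly yields a wrong H3c estimate, or that the product will be too small because people whose inhibition suffers most from sleep loss also depend on it most. The documents support neither: no slope covariance is given, and its sign is unknown. A reader might also infer that the indirect and direct effects would fail to sum to the H3b total. SA is binary, and that additivity belongs to a linear or latent scale, so the claim should not be made. On the probability scale neither the product nor the product plus covariance is the mediated effect.

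**Conclusion.** The point holds conditionally. If both mediating slopes are random and they covary, a path product does not estimate the average within-person indirect effect that H3c asks about, on the latent linear scale. The error can go either way. Over the assumed range it is negligible when slopes vary little between persons and can equal or exceed the effect itself when they vary as much as their mean or more. Nothing in the article says where in that range the study will fall. Because H3c is exploratory and is the only hypothesis for which the plan derives an indirect effect, the point is minor. No other analysis is affected.

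**What to change.** In the H3c part of the Data Analysis Plan, replace the sentence on the indirect-effect command with a rule that matches the fitted model:

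- **Default.** Hold the inhibitory-control-to-SA slope fixed across persons, keep the sleep-to-inhibitory-control slope random, and report the posterior of the product with its 95% credibility interval. The small number of expected attempters supports this choice.
- **If both slopes are kept random.** Estimate their between-person covariance and report the posterior of mean(a) × mean(b) + cov(a,b) with its 95% credibility interval.

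In either case, state that the effect is on the latent scale of the binary SA outcome.

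The cost is a sentence or two in the plan and a few lines of model code, with no change to data collection. The default assumes that all participants share one inhibitory-control-to-SA slope, which should be stated as an assumption. The alternative avoids that assumption at the price of a wider interval.
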